## Abstract

**Background:**

The loss of functional ability of patients after stroke is mostly caused by dysfunction of the upper limbs, especially the hands. Hand functional exercise is the premise of alleviating hand dysfunction, and the relief of hand spasm is the basis of timely and effective hand functional exercise. Previous clinical observation have shown that fascial-point needling can effectively alleviate hand spasm immediately after stroke, but further evidence from large-sample studies is needed. The overall objective of this trial is to further evaluate the clinical efficacy of fascial-point acupuncture on hand spasm after stroke.

**Methods/design:**

This multicenter randomized controlled trial will compare the efficacy of fascial-point acupuncture versus sham acupuncture and routine rehabilitation therapy in stroke patients with hand spasm. Patients will be randomized to undergo either the fascial-point acupuncture, the sham acupuncture or the control (routine rehabilitation therapy). We will recruit 210 stroke inpatients who meet the trial criteria and observe the remission of hand spasm and improvement of limb function after 4 weeks of intervention. The first evaluation indices are the remission of hand spasm and the duration of spasm remission. The second evaluation indices are the hand function of the affected limbs and the activities of daily living. When the accumulative total number of cases included reaches 120, a mid-term analysis will be conducted to determine any evidence that experimental intervention does have an advantage.

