### Sample size

Our study will be designed as a randomized controlled trial, and the main outcome is whether hand spasm after stroke is relieved after treatment. Current experience shows that the previous effectiveness rate of conventional acupuncture treatment is about 50%, and the expected effectiveness rate is 85%. The significance test level is 0.05, and the test power is 0.9. Sample size is calculated by using:

$$ \mathit{\mathsf{N}}={\left(\mathit{\mathsf{U}\mathsf{\alpha }}+\mathit{\mathsf{U}\mathsf{\beta }}\right)}^{\mathsf{2}}\times \mathsf{2P}\left(\mathsf{1}-\mathit{\mathsf{P}}\right)/{\left(\mathit{\mathsf{P}\mathsf{1}}-\mathit{\mathsf{P}\mathsf{0}}\right)}^{\mathsf{2}}, $$

where, *N* is the required sample size for each treatment group, and the sample size of each group is equal. When *α* is 0.05 and *β* is 0.1, the normal distribution quantile table shows that:
$$ \mathit{\mathsf{U}\mathsf{\alpha }}\left(\mathsf{0.05}\right)=\mathsf{1.65},\mathsf{and} $$
$$ \mathit{\mathsf{U}\mathsf{\beta }}\left(\mathsf{0.1}\right)=\mathsf{1.28}. $$

*P0* and *P1* represent the original curative effect and the expected curative effect, 50% and 85%, respectively. By substituting the above parameters and values into the formulas, 63 cases will be needed for each group. Accounting for a 10% expulsion rate, the final estimated sample size will be about 70 cases per group (210 in total).

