### Data analysis

#### Statistical analysis

Statistical analysis of research data will be performed by health statisticians and major researchers using SPSS or SAS. Pearson’s *χ*2 test or Fisher’s exact test will be used to analyze classified variables and continuous variables will be evaluated using Student’s *t* test or an appropriate non-parametric method. All statistical tests will be double-sided. The statistical significance level will be set at 5%. The measured data will be described by mean ± standard deviation. Before the analysis, the normality test and homogeneity test of variance will be carried out. If the normal distribution is satisfied, a *t* test will be used. The LSD or SNK method will be used for multiple comparisons, and the rank sum test will be used for non-normality or non-uniformity of variance.

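### An efficacy interim at 120 of 210 patients sits beside one flat two-sided 5% level; if both looks use it and either can be claimed, type I error is about 8.1% per comparison

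*Protocol article*

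**What the plan says.** The interim appears only in the methods paragraph of the abstract. Its trigger is "When the accumulative total number of cases included reaches 120", against a planned total stated as "We will recruit 210 stroke inpatients". Its purpose is efficacy, not safety or feasibility: "a mid-term analysis will be conducted to determine any evidence that experimental intervention does have an advantage".

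The Statistical analysis section gives the rules for testing: "All statistical tests will be double-sided" and "The statistical significance level will be set at 5" per cent. It names no exception to that level and does not mention the interim. The LSD or SNK procedure it names is for comparisons between groups, not for repeated looks over time.

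The Sample size section uses the same level ("The significance test level is 0.05, and the test power is 0.9") and makes no allowance for an earlier look.

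**The concern.** A second opportunity to declare success, tested at the same level as the first, raises the false positive rate above that level. The only level the article offers is 5%. An analyst working from the published text would most naturally apply it at 120 patients and again at 210.

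Error control for the primary conclusion is at stake. The boundary also cannot be chosen credibly once interim results are known, so it has to be settled before then.

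**Working it through.** **Inputs from the article**
- Interim at 120 patients, final at 210 (abstract). The total follows from the Sample size section: 63 / 0.9 = 70 per group, and 3 x 70 = 210. Whether 63 itself follows from the stated formula is a separate question. The result below depends on the ratio 120/210, not on how 63 was obtained.
- Two-sided 5% level (Statistical analysis), so the critical value is 1.96.

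**Assumptions the article does not state**
- The interim is tested at 5%.
- A positive result at either look can be claimed.

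**Plan's own figure.** With one look, P(|Z| > 1.96) = 5.0%. The stated level is correct for a single final analysis.

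**Two looks**
1. Information fraction t = 120/210 = 0.571.
2. Under the null hypothesis the interim and final statistics Z1 and Z2 are bivariate normal with correlation sqrt(0.571) = 0.756.
3. P(|Z1| > 1.96 and |Z2| > 1.96) = 0.0194.
4. P(either exceeds 1.96) = 0.05 + 0.05 - 0.0194 = 0.0806, or **8.06%**.

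**Sensitivity to the inputs**

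| Setting | Overall type I error |
|---|---|
| t = 120/189 = 0.635 (189 = 3 x 63, final count after dropout) | 7.83% |
| t = 120/210 = 0.571 | 8.06% |
| t = 0.50 | 8.31% |
| t = 0.40 | 8.63% |
| t = 0.571, one-sided 5% at both looks (the 1.65 used in the Sample size section) | 7.77% |

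**What restores 5%, at t = 0.571**
- O'Brien-Fleming-type (Lan-DeMets) spending, 0.025 in each tail. The tail area spent at the interim is 2 x [1 - Φ(2.241/0.756)] = 2 x [1 - Φ(2.965)] = 0.0030. The interim bound is therefore 2.745 (two-sided p = 0.0061). Solving for the final bound that gives 5% overall yields 1.977 (p = 0.0481).
- Spending the whole 0.05 in one piece with the same function gives 0.0095 and 0.0463. Both versions hold 5%, so the convention has to be named.
- Interim p < 0.001 with the final at 5% gives 5.01%.
- No efficacy claim or stopping at the interim leaves the final test at 5%.

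**Effect of the trigger.** If the bounds 2.745 and 1.977 were applied when the interim really held half, or 40%, of the information, the overall error would be 5.05% or 5.13%. Counting patients without the outcome therefore matters little to the error.

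**The case against.** The strongest reply is that this is a condensed journal article. Boundaries, alpha spending and interim procedures are commonly left to the full protocol or the SAP, neither of which is shown. The interim has one sentence in the abstract, and reading the analysis section's 5% as the interim level is an interpretation.

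Much of this stands. A missing boundary alone would be no finding. A reader might infer that the trial's real type I error is 8%. The article does not support that, because it never says that the interim is tested at 5% or that a positive look can stop the trial or be claimed. A strict interim bound would give 5.01%, and a look with no consequences would give 5%.

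The reply does not remove the inconsistency in what is printed. The article announces a look for advantage and then sets one level without exception. A boundary held in another document would have to depart from that level at the interim, the final, or both.

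A reader might also multiply the error over three pairwise comparisons and two primary indicators and quote a much larger family rate. That would treat every pairwise test as unprotected, although the analysis section names LSD or SNK for group comparisons. It is also a separate issue that would exist without any interim.

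The trigger counts patients included, and the latest of them will not yet have a week-4 result. The article does not say that they would be analysed without it, so this is imprecise wording and not a demonstrated error.

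**Conclusion.** The point holds in conditional form. The article plans an efficacy look at 57% of the sample and fixes a flat two-sided 5% level with no allowance for it. If both looks use that level and either can be claimed, type I error is 8.06% per comparison and endpoint, about 3 percentage points above the stated level. Over plausible information fractions it lies between 7.8% and 8.6%. The calculation assumes approximately normal test statistics and information proportional to the number of patients. Whether the inflation would occur depends on an interim rule that the article does not give.

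**What to change.** Before any interim data are seen, add to the Statistical analysis section one of the following:

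1. An efficacy boundary that holds 5% overall, for example O'Brien-Fleming-type spending with 0.025 per tail: interim two-sided p < 0.006 and final p < 0.048 at 57% information.
2. Interim p < 0.001 with the final at 5% (overall 5.01%).
3. A statement that the interim will lead to no efficacy claim and no stopping, with the final test at 5%.

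Under any option, bring the single-level sentence into line with the rule chosen. Define the interim count as 120 patients with the week-4 outcome, so that the information fraction matches the boundary.

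The cost is a few sentences. Option 1 lowers the final level from 0.05 to about 0.048, with negligible loss of power. Options 2 and 3 leave it unchanged. Counting completed outcomes delays the interim by roughly the 4-week treatment period.

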### Recruitment

Recruitment of patients began on 1 June 2019 and will be completed in June 2021, or after the required number is obtained, whichever is earlier. We will develop plans and methods to contact subjects, including the preparation of informed consent, obtaining necessary data, videos and pictures to help subjects understand the purpose and program of the trial. We will also explain to the subjects the advantages and disadvantages of the treatment and the relevant safety measures to be taken during the trial. In addition, we will post recruitment posters in and around the hospital, or use the Internet for recruitment. According to the inclusion/exclusion criteria, the research team will preliminarily judge the possibility of each subject’s inclusion, and conduct the relevant examination on them after they have signed the informed consent, and finally confirm whether the subjects actually meet the inclusion/exclusion criteria according to the examination results.

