### Randomization

After signing the informed consent, participants will be randomly divided into three groups: an acupuncture group, a sham acupuncture group and a control group. Randomization will be accomplished by qualified researchers using randomization software to generate random-number sequences. In the process of randomization, allocation should be kept hidden. All patients will be randomly divided into groups in a ratio of 1:1:1. The strips revealing treatment allocation will be placed in sealed opaque envelopes with sequential numbers. After obtaining informed consent, the envelopes will be opened in turn. Patients and data analysts are not clear about the randomized grouping.

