## Discussion

The timely relief of spasticity in stroke patients is particularly important for the rehabilitation of limb function, so it is a key step to apply effective treatment measures to relieve spasticity as much as possible. A preliminary clinical observation of 16 cases of hand spasm after stroke treated by fascial-point acupuncture has been completed in our group. The results show that fascial-point acupuncture can effectively alleviate hand spasm immediately after stroke. However, its cumulative effect, duration of spasm relief and long-term efficacy need further clinical study. Hence, here we propose a multicenter, prospective and randomized clinical trial to further evaluate the clinical efficacy of fascial-point acupuncture in relieving hand spasm after stroke.

In order to eliminate the interference of acupuncture itself on the experimental results, a sham acupuncture group will be established in this study. However, bias exists in all clinical trials. In our trial, the blindness of the acupuncturists and patients in designing a randomized controlled trial involving acupuncture manipulation will be the most challenging aspect. Therefore, surface EMG measurements are also used as part of the outcome assessment in addition to the scales used in previous studies. In recent years, EMG has been widely used in spasticity assessment, especially after stroke [26]. The application of electrophysiological measurement can provide quantitative information of spasticity and reduce the interference of subjective factors in scale evaluation. In addition, the multicenter development of the study is also related to biases, mainly including differences in acupuncture techniques. We tried to eliminate these biases by examining the needling procedures of other participating hospitals and training acupuncturists in all participating centers. We firmly believe that the results of this study will help to lay a foundation for the alleviation of hand spasm after stroke and functional improvement.

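### The efficacy look at 120 of 210 patients falls under an analysis rule that includes trial researchers, and nothing keeps its result from those who recruit and treat the rest

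*Protocol article*

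**What the plan says.** The interim look appears once, in the abstract (Methods/design) of the protocol article: when 120 patients have been included, "a mid-term analysis will be conducted to determine any evidence that experimental intervention does have an advantage". The planned total is in the same paragraph: "We will recruit 210 stroke inpatients who meet the trial criteria". The body of the article does not return to the look.

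Four other places bear on it:

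- **Statistical analysis**, the only rule on who analyses: "Statistical analysis of research data will be performed by health statisticians and major researchers using SPSS or SAS". The interim is neither named nor excepted.
- **Randomization**: "Patients and data analysts are not clear about the randomized grouping".
- **Outcome measures**: evaluation is by one team member blinded to allocation.
- **Study setting**: the lead hospital, which is one of the three recruiting and treating sites, is also responsible for trial coordination and data management.

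On the staff in contact with patients, Recruitment says "We will also explain to the subjects the advantages and disadvantages of the treatment", and the Discussion concedes that "the blindness of the acupuncturists and patients in designing a randomized controlled trial involving acupuncture manipulation will be the most challenging aspect".

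**The concern.** A comparative look while recruitment is open is safe for the remaining patients only if its result stays with people who have no contact with them. Here the stated analysis team includes the trial's own major researchers, and the question set for the look is directional. Followed as written, researchers would read whether the experimental arm is ahead while a large part of the sample has yet to be enrolled and treated.

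This trial is more exposed than most:

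- The needling depends on the operator. Under Intervention, manipulation continues until the physician feels a particular resistance, so effort can change with belief.
- Control patients receive no needle and can work out their allocation. What staff tell patients can therefore shape expectation.
- The hand-spasm score is a judged scale.

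If knowledge of the leading arm alters presentation or delivery, patients enrolled before and after the look are no longer treated alike. The final analysis has no dependable way to correct that.

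This point is separate from the significance level used at the look and from how complete the data are at that time.

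**Working it through.** **1. Patients affected.** Inputs: 120 and 210 (abstract) and 1:1:1 allocation (Randomization).

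- Left to enrol at the trigger: 210 − 120 = 90, and 90/210 = 42.9%.
- Per arm: 120/3 = 40 included and 90/3 = 30 to come.
- Information fraction if all 120 have outcomes: 120/210 = 0.571.

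**2. If the look waits for outcomes.** The trigger counts patients included, not patients with outcomes. Assume even accrual that does not pause. The article gives two enrolment lengths: 24 months (two years, to June 2021) and about 28 months (June 2019 to October 2021). Rates are 210/24 = 8.75 and 210/28 = 7.5 per month. The wait for the last of the 120 is 28 days = 28/30.44 = 0.92 month for the 4-week outcome, or 6.92 months to the end of follow-up.

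| Look takes place | Left to enrol, 24 months | Left to enrol, 28 months |
|---|---|---|
| At the trigger | 90 | 90 |
| After 4-week outcomes | 90 − 8.0 = 82 | 90 − 6.9 = 83 |
| After 6-month follow-up | 90 − 60.5 = 29.5 | 90 − 51.9 = 38 |

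So 90 is the maximum, and roughly 30 remain even after the longest wait.

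**3. Would the look show a leader?** Use the planning rates under Sample size (50% and 85%), 40 per arm, two-sided 5%, normal approximation, all 120 evaluable.

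- Mean rate 0.675. Null SE = √(2 × 0.675 × 0.325/40) = 0.1047.
- Alternative SE = √((0.25 + 0.1275)/40) = 0.0971.
- z = (0.35 − 1.96 × 0.1047)/0.0971 = 1.49, so power is about 93%.

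The 50% is the article's rate for conventional acupuncture. Applying it to the sham or control arm is an assumption. On those rates the look would very likely identify the leading arm.

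**4. Roles side by side.**

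| Section | What it fixes | What it leaves open |
|---|---|---|
| Abstract | A directional comparison at 120 | Who runs it, who reads it |
| Statistical analysis | Analysts include major researchers | Whether the interim is included; whether these researchers also recruit or treat |
| Randomization | Analysts do not know the grouping | How a blinded analyst can report that the experimental arm has an advantage |
| Outcome measures | Assessor blinded to allocation | Whether the assessor learns the interim result |

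Coded arms protect the analyst while the comparison is run. To answer the question asked, someone must then link the code to the experimental arm, and from that moment direction is known to whoever reads the answer.

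**5. Illustration only: can the damage be sized?** Suppose a bias of d SD enters one contrast in the last 30 of 70 patients per arm. The z-shift is (30/70) × d × √(70/2), which is 0.254, 0.507 and 0.761 for d = 0.1, 0.2 and 0.3. The two-sided error of a nominal 5% final test, under a true null, then depends on when the bias arises:

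| Bias arises | d = 0.1 | d = 0.2 | d = 0.3 |
|---|---|---|---|
| Whatever the look shows | 5.7% | 8.0% | 11.8% |
| Only after a significant favourable look | 5.4% | 5.7% | 6.0% |
| After any favourable lead | 6.9% | 9.7% | 13.6% |

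Neither d nor the mechanism is in the article. The spread from 5.4% to 13.6% shows that no single figure can be quoted.

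**The case against.** **Analysts are stated to be blind.** This is the best counter-argument. A comparison can be run on coded arms, and the code opened only by someone outside the team; the article does not exclude that. What stands is that the team learning the leader is a likely consequence of the text and not something the text says. What does not stand is that analyst blinding settles the matter, because the look's question cannot be answered without identifying the experimental arm.

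**The assessor is blinded.** This carries weight. An assessor who does not know a patient's allocation cannot favour an arm, even knowing that it leads. The risk to scoring is therefore secondary, provided the result does not reach the assessor. Blinded scoring does nothing for consent discussions, operator effort or patient expectation.

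**A fuller document may cover it.** A full protocol, analysis plan or charter may say who sees the result. Silence alone would be no finding in a condensed article. Here, though, the published text positively gives analysis to trial researchers and fixes a directional look during enrolment.

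**Stronger readings to avoid.** A reader might infer that patients will be recruited with a one-sided account of benefit, but Recruitment promises disadvantages as well as advantages. A reader might also infer that the article declares the acupuncturists unblinded; the Discussion says only that blinding them is the hardest part, although unblinded needling is likely in practice.

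**Conclusion.** The point holds in a limited form. The abstract, Randomization and Statistical analysis do not fit together: a directional efficacy look is planned during recruitment, the analysts include trial researchers, the analysts are also said to be blind, and no stated rule keeps the answer from those who recruit and treat.

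The exposed group is 90 of 210 patients (43%) at the trigger, about 82 to 83 if the look waits for 4-week outcomes, and about 30 to 38 if it waits for full follow-up. The last two ranges assume even, uninterrupted accrual. The main threat is to how treatment is presented and delivered.

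The documents do not support saying that the team will certainly learn which arm leads, nor attaching an inflated error rate. The rates in the working are illustrations and carry no weight in the conclusion. The change should be made before the look, because bias that follows disclosure cannot be reliably removed afterwards.

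**What to change.** Reconcile the three sections by stating that:

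1. the health statistician alone runs the interim analysis;
2. only the decision to continue or stop the trial is passed on;
3. before database lock, no arm-level result reaches anyone who recruits, treats, scores or manages data;
4. the major researchers' part in the analysis begins after lock.

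Optionally, add a descriptive table of the treatment effect in patients enrolled before and after the look. It is a check for a visible shift and does not correct for one.

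The cost is a few sentences and, if wanted, one table. No new post is needed, because health statisticians are already named. The downside is small: the investigators do not see interim figures.

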**Discussion:**

Our aim is to evaluate the efficacy of fascial-point acupuncture in relieving hand spasm after stroke. The results should provide more evidence for the clinical application of this therapy in the future.

**Trial registration:**

Chinese Clinical Trial Registry (ChiCTR), ID: ChiCTR1900022379. Registered on 9 April 2019

## Background

With the advent of an aging society, the incidence of stroke is increasing year by year [1]. In recent years, due to the progress of science and technology and the continuous development of medicine, the survival rate and survival time of stroke patients have been greatly improved and prolonged, but the disability rate is still high [2]. The loss of activities of living of patients after stroke is mostly caused by upper-limb dysfunction, especially hand dysfunction [3]. Hand functional exercise is the premise of alleviating hand dysfunction, and the alleviation of hand spasm is the basis for timely and effective hand functional exercise. Hence, alleviating hand spasm after stroke has far-reaching significance in reducing disability rate and improving the daily activities of living of patients. At present, the main methods to relieve the increased muscle tension after stroke are drug intervention and non-drug therapy (such as physical factors and kinesiotherapy) [4, 5]. Sometimes, traditional Chinese medicine, acupuncture, massage, brace, orthosis and use of a rehabilitation robot are used as adjuvant therapy [6, 7]. Each therapy has its own advantages and disadvantages.

Drug intervention mainly includes using central antispasmodic drugs and peripheral-nerve local-blocking antispasmodic drugs. Current clinical applications have achieved some positive results. The use of central antispasmodic drugs is relatively simple and convenient, but long-term use will likely lead to obvious drug resistance and related adverse reactions, such as muscle weakness, nausea, mental depression, etc. In clinical application, drug replacement and dosage adjustment should be often considered. Botulinum toxin A is the representative of peripheral-nerve local-blockade antispasmodics. However, botulinum toxin A can only be used as a component of a multidisciplinary combination to alleviate the increase of limb-muscle tension after stroke. Other therapies are often needed in clinical application. In addition, in view of the technical difficulties and high cost of the clinical implementation of botulinum toxin A, it has not been widely carried out in the clinic to alleviate the increase of limb-muscle tension after stroke [8, 9]. Physical therapy is mainly divided into exercise therapy, manipulation therapy and physical factor therapy. Exercise therapy and manipulation therapy can inhibit and weaken spasticity-inducing factors in patients with post-stroke limb spasm, so that limb movement control and motor function can be significantly strengthened and improved. However, a longer intervening time should be guaranteed in the treatment of post-stroke limb spasticity, and the individual condition of the patients should be taken into account in clinical practice [10, 11]. In order to reduce the adverse effects caused by excessive exercise, we should adjust the range, intensity, frequency, and course of training. Physical factor therapy includes paraffin therapy, hydrotherapy, repetitive transcranial magnetic stimulation, biofeedback therapy, functional electrical stimulation and shock-wave therapy. Physical factor therapy has been widely used in the treatment of limb spasm after stroke, and has achieved certain effects, but its exact mechanism is still unclear, and there is a lack of evidence-based medical evidence for large-sample clinical research. In addition, the implementation of physical factor therapy has not yet been standardized or clinical guidelines set; the operation depends on personal preferences and experience, and the intensity of stimulation and dose in different clinical reports varies [12–16]. Orthosis and rehabilitation robots, with their good sustainability and rhythm, can assist in alleviating hand spasm after stroke and reduce the workload of therapists to some extent, but their sensitivity and regulation ability are poor, and they are expensive. They also require space and related technical personnel, which is not conducive with their clinical promotion [17, 18]. Although many positive results have been achieved in the study of traditional acupuncture and massage in the treatment of post-apoplectic limb spasm, it is often necessary to select multiple acupoints to achieve a curative effect. Also, the acupoints selected by each research group are different, which is not conducive with its clinical promotion [19]. Moreover, the criteria, principles and operating essentials of massage manipulation need to be unified and standardized, and its mechanism needs urgent clarification. All these circumstances encourage us to seek more simple, convenient, effective and inexpensive forms of rehabilitation therapy.

At present, the existence of myofascial trigger points has been widely accepted [20]. The myofascial trigger point is a common hand-spasm factor in stroke patients. In long-term rehabilitation clinical practice, the team found that physicians could touch a cord-shaped nodule as the most obvious sore point of the patient’s discomfort, i.e., the fascia point to be needled, by pressing between the first and second metacarpal bones on the dorsal of the patients with hand spasm after stroke from the far side to the proximal side with thumb pulp. Preliminary clinical observation of 16 patients with hand spasm after stroke treated by fascial-point acupuncture has been completed in our group. The results show that fascial-point acupuncture can effectively alleviate hand spasm immediately after stroke, but its cumulative effect, duration of spasm relief and long-term efficacy need further clinical research [21]. Therefore, we suggest that this multi-site, prospective clinical trial be carried out to further evaluate the clinical efficacy of fascial-point acupuncture in relieving hand spasm after stroke.

